
### Phase II: randomized controlled trial to test the effectiveness of the psychoeducational intervention

**Study design:** a randomized controlled trial with an allocation ratio of 1: 1 will be utilized.

**Study setting:** 1) University College Hospital (UCH), Ibadan, Nigeria: it serves as a referral tertiary center for Nigeria and sub-Saharan Africa. The study will be at the outpatient gynecology clinic of the hospital; 2) Adeoyo Maternity Hospital (AMH), Yemetu, Ibadan, Nigeria: this is a province-owned secondary health care facility.

**Study subjects:** women attending gynecology clinics in UCH or AMH on account of infertility. Consenting participants will be randomized into the intervention and control arms of the study, respectively.

**Eligibility criteria:** women aged 18 years and above, who have been trying to conceive for at least one year, and who do not have any children.

**Interventions:** consecutive, eligible infertility clinic attendees will be invited to participate in the study and informed consent obtained. Sociodemographic data would be collected via a structured questionnaire. Baseline assessment on participants' psychological and emotional state will be collected via Hospital Anxiety and Depression Scale (HADS) [28]. Thereafter, the participants will be allocated into study groups. Participants in the intervention arm will attend the intervention session on a specified date at the facility. The psychoeducational video will be viewed, and immediate feedback will be obtained. Participants in the control arm will also receive the usual treatment offered all attendees at the gynecology clinics - comprising health talks by public health nurses and explanations and counselling provided by the managing physicians. The study´s primary outcomes are depressive and anxiety symptoms. HADS is a self-assessment scale which has subscales that measure severity of anxiety and depression. It is validated for use in medical outpatient clinics. Participants are followed up at three and six weeks; HADS will be administered at both times. Participants will be counseled on the need for follow-up. Recruited respondents in both arms will receive phone call reminders ahead of scheduled clinic appointments to improve attendance and minimize loss to follow-up.

**Sample size estimation:** the minimum sample size was determined using the formula for comparing two means i.e.

$$\text{n=}\frac{2{\left[Z_{1-\alpha /2}+Z_{1-\beta }\right]}^{2}}{\Delta^{2}}$$

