where Δ, effect size =

$$\Delta =\frac{\mu_{1}-\mu_{1}}{\sigma }$$

where Z1-α/2 [α] was set at 5% i.e. 1.96; Z1-β [β] was set at 20% i.e. power at 80% = 0.84 [29]. A moderate effect size of 0.53 was used. A minimum sample size of 57 was calculated. Attrition rate of 20% was incorporated in the calculation and sample size was estimated at 68 women in each group.

**Randomization procedure:** a randomization list of randomly permuted blocks of treatment assignments in blocks of 4 will be prepared by the study statistician, using a computer-generated table of random numbers. The research assistant will open the sealed envelope containing the assigned group after baseline HADS has been administered. The clinical staff recruiting participants and the data analyst will be blinded, as he will receive two spreadsheets of data without knowing which is the intervention arm.

**Data management and analysis:** the data collected will entered into the computer and analysed using IBM SPSS version 23.0. Interim analysis will be carried out using Mann-Whitney-U test to compare independent samples of the intervention and control groups at 0, 3 and 6 weeks. Survival analysis will also be carried out at each time to assess number of cases of depression or anxiety that transited to non-cases (Figure 1). A data monitoring committee is not necessary as there are no interventions bordering on patient safety. There are no issues that might necessitate termination of trial. Malfeasance or adverse events are not applicable in a trial that constitutes audiovisual expert education as the intervention.

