		Cases No. [%]	Non-cases No. [%]	Cases No. [%]	Non-cases No. [%]	Cases No. [%]	Non-cases No. [%]	Cases No. [%]	Non-cases No. [%]
Age	< 35 years								
	≥ 35 years								
Marital status	Married								
	Unmarried								
Education	None								
	Primary/ secondary								
	Tertiary								
Occupation	Unemployed								
	Unskilled								
	Skilled								
Previous pregnancy	Yes								
	No								
Identified cause of infertility	Self								
	Male partner								
	Both/ unknown								
Length of infertility	< median								
	≥ median								
Average monthly family income	< median								
	≥ median								

**Table 3 T3:** comparison of the HADS scores between intervention and control groups at 0, 3 and 6 weeks

	HADS at baseline				HADS at 3 weeks				HADS at 6 weeks			
	Intervention group	Control group	X^2^ test	p-value	Intervention group	Control group	X^2^ test	p-value	Intervention group	Control group	X^2^ test	p-value
Cases												
Non-cases												
Total												

X2 test: Chi square test

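### The planned Mann-Whitney comparisons at 3 and 6 weeks are not adjusted for baseline HADS, although it is collected before allocation is revealed, so they give up precision

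*Protocol article*

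**What the plan says.** All references are to the Phase II part of the protocol article.

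- **Outcome and timing (Interventions).** The "primary outcomes are depressive and anxiety symptoms", measured on the HADS subscales. Baseline is covered: "Baseline assessment on participants' psychological and emotional state will be collected via Hospital Anxiety and Depression Scale (HADS"). Follow-up is at two visits: "Participants are followed up at three and six weeks; HADS will be administered at both times".
- **Order of baseline and allocation (Randomization procedure).** "The research assistant will open the sealed envelope containing the assigned group after baseline HADS has been administered".
- **Comparison of arms (Data management and analysis).** The stated method is a "Mann-Whitney-U test to compare independent samples of the intervention and control groups at 0, 3 and 6 weeks", introduced as interim analysis.
- **Second analysis (same paragraph).** "Survival analysis will also be carried out at each time to assess number of cases of depression or anxiety that transited to non-cases".
- **Results layout (Table 3).** The title announces a "comparison of the HADS scores between intervention and control groups at 0, 3 and 6 weeks". The rows count cases and non-cases, with a separate chi-square test and p-value at each of the three times.

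The article states no covariate, change score or repeated-measures model.

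**The concern.** A HADS score taken before allocation is revealed cannot be affected by the arm, and it is usually the best single predictor of the same woman's later score. The plan collects it and then does not use it in the score comparison. Instead it tests baseline itself between the arms, twice: by Mann-Whitney at week 0 and by chi-square in Table 3. Any difference at that point is due to chance, because the arms are formed at random, so these tests answer no question.

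The third aim of the study is to evaluate effectiveness. An unadjusted comparison has less power for that aim than an adjusted one using data already in hand. If the arms happen to differ at baseline, part of that difference carries over into the week-3 and week-6 comparisons. Randomisation is described as permuted blocks of 4, with no stratification by baseline HADS, so nothing in the stated design limits such an imbalance.

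**Working it through.** **Inputs from the protocol article (Sample size estimation).** Effect size 0.53 SD; two-sided alpha "was set at 5% i.e. 1.96"; power 80% (z = 0.84); 57 per group before attrition; 20% attrition; 68 per group.

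**Assumed, not in the documents.** Correlation r between baseline and follow-up HADS, taken from 0.3 to 0.7, and roughly normal scores.

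**Step 1: the plan's own figure.**
n = 2(1.96 + 0.84)² / 0.53² = 15.68 / 0.2809 = 55.8, so 56 against the stated 57, which agrees closely. 57 × 1.2 = 68.4 gives the stated 68. The formula has no correlation term, so the plan was sized for an unadjusted comparison. If 20% of 68 are lost, 68 × 0.8 = 54.4, so about 54 per group are analysed.

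**Step 2: the planned test at 54 per group.**
For normal data the Mann-Whitney test has efficiency 3/π = 0.955 relative to the t-test. The effective n is 54 × 0.955 = 51.6. With the noncentral t and d = 0.53, power is 76.0%. An unadjusted t-test on 54 per group has 77.9%, so about 2 points of the gap to the adjusted analysis come from the rank test and not from the lack of adjustment.

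**Step 3: the adjusted comparison at 54 per group.**
Adjustment multiplies the residual variance by 1 − r² and the standard error by √(1 − r²). The effective effect is 0.53 / √(1 − r²).

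| r | √(1 − r²) | Cut in standard error | Effective effect | Power |
|---|---|---|---|---|
| 0.3 | 0.954 | 5% | 0.556 | 81.6% |
| 0.4 | 0.917 | 8% | 0.578 | 84.6% |
| 0.5 | 0.866 | 13% | 0.612 | 88.3% |
| 0.6 | 0.800 | 20% | 0.663 | 92.7% |
| 0.7 | 0.714 | 29% | 0.742 | 96.9% |

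A simulation at the pre-attrition 57 per group (3,000 trials per setting) agrees: Mann-Whitney 78% to 79%; ANCOVA 84%, 90% and 97% at r = 0.3, 0.5 and 0.7.

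**Step 4: validity of the planned test.**
In the same simulation with no true effect, Mann-Whitney rejected in 4.2% to 5.2% of trials and ANCOVA in 4.4% to 5.3%. Averaged over randomisations, the unadjusted test keeps its error rate.

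**Step 5: what a given imbalance does.**
At 57 per group the baseline difference has standard error √(2/57) = 0.187 SD, so its 95% range is ±1.96 × 0.187 = ±0.37 SD. A baseline difference of D shifts the expected unadjusted follow-up difference by r × D. Given D, the unadjusted test statistic has mean r × D × √(n/2) and variance 1 − r². At the edge of the range, D = 0.37:

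| r | Shift (SD) | Type I error given this imbalance |
|---|---|---|
| 0.3 | 0.11 | 8% |
| 0.5 | 0.19 | 13% |
| 0.7 | 0.26 | 21% |

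In the simulated null trials whose imbalance exceeded 0.30 SD (about 11% of them), false positives were 8%, 10% and 20% for Mann-Whitney at r = 0.3, 0.5 and 0.7, against 5%, 3% and 5% for ANCOVA.

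**The case against.** Several points on the other side have force.

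- **Baseline is not wholly unused.** A reader might infer that the plan ignores baseline HADS. It does not: the survival analysis follows cases that become non-cases, which conditions on baseline case status. That reduces the score to two categories and does not adjust the score comparison, so the point about the Mann-Whitney tests stands.
- **The status of the test is unclear.** The text labels it interim, names no analysis as final, and does not name the variable tested. Reading it as a comparison of visit-wise scores is an inference. It is the natural one, because a change score cannot be tested at week 0. The tests also include the six-week visit, and no other score-type comparison is given.
- **The planned test is not biased.** A reader might take chance imbalance to mean systematic error. Step 4 shows otherwise. The loss is in precision, and in error conditional on the imbalance that occurs. The sample size also assumed an unadjusted comparison, so design and analysis are broadly consistent.
- **The size of the gain rests on an assumed correlation.** At r = 0.3 it is modest. HADS subscale scores may also be skewed, which would weaken the normal-data comparison.
- **Mann-Whitney does not rule out an effect estimate.** It can be paired with a Hodges-Lehmann shift and interval. Whether that is reported, and how missed visits are handled, are details an article commonly leaves to a fuller document. Neither is counted against the plan here.
- **The trial is described as exploratory**, so this is a matter of efficiency and not of validity.

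The possibility that a statistical analysis plan exists does not remove the point. The article itself fixes the test and the visits, so the point concerns a stated choice and not an omission.

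**Conclusion.** The point holds as one of efficiency and of exposure to chance imbalance. The stated comparison of arms is unadjusted although a baseline score unaffected by allocation is in hand, and the week-0 comparisons between arms are uninformative. If r lies between 0.3 and 0.7 and scores are roughly normal, baseline adjustment lowers the standard error by 5% to 29% and raises power at 54 per group from about 76% to between 82% and 97%. The correlation is an assumption, and at its lower end the gain is small. The documents do not support saying that the planned test is invalid or biased, that baseline is ignored altogether, or that no effect estimate could be obtained. The change is worth making because the planned test falls a little short of the intended 80% power once attrition is allowed for, and the remedy is cheap.

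**What to change.** Make the main comparison of the week-3 and week-6 HADS scores baseline-adjusted, separately for the anxiety and depression subscales. Either of two forms will do:

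- ANCOVA at each visit, with arm and baseline subscale score; or
- a mixed model for repeated measures with arm, visit, arm-by-visit and baseline subscale score, using all women with at least one follow-up score. A woman with no follow-up score contributes nothing to this model, so it should not be described as including everyone randomised.

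Report the adjusted mean difference in HADS points with a 95% confidence interval at each visit. Keep the week-6 Mann-Whitney test as a sensitivity analysis in case the scores are skewed. Drop the week-0 comparison between arms and describe baseline HADS by arm instead. State whether the comparisons now labelled interim are the final analysis.

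The cost is a change of wording in the analysis plan and slightly more analysis work. No new data, visits or participants are needed.

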**Figure 1 F1:**
[figure not shown]
program evaluation and review technic (PERT) diagram showing flow of participants into cases or non-cases

**Ethical considerations:** ethical approval was obtained from the University of Ibadan/University College Hospital Ethical Committee (Ref: UI/EC/17/0003). Protocol amendments will be communicated to the ethics committee and written approval obtained before commencing. Clinical care providers in the clinic will recruit the participants and obtain assent, then a trained research assistant will obtain informed consent (Annex 1). Anonymized data will be obtained from participants in privacy and data collected will be kept in a secure locked cabinet in an office. Data entered on to the study computer will be password-protected. Personal information will only be recorded in order to send reminders and invitations for follow up sessions. The investigators will have access to the final data set and will not disclose information to other parties.

**Trial registration:** the trial is registered with Pan African Clinical Trial Registry [PACTR201901892865101].

**Reporting of trial results:**Table 1 will describe the demographics of the participants in the intervention and control groups, while Table 2 will show the proportion of cases to non-cases. The changes in these over 6 weeks will be documented in Table 3 and Figure 1. Trial findings will be communicated in a written report to sponsors, presented at a gynecology conference and published in a per-reviewed journal. The authors will be those who have contributed to the conception, design, data acquisition and writing of the manuscript. The full protocol and dataset will be available by contacting the corresponding author.

**Table 1 T1:** distribution of socio-demographic characteristics of participants

Variables	Classes	Intervention group No [%]	Control group No [%]	p-value
Age	< 35 years			
	≥ 35 years			
Marital status	Married			
	Unmarried			
Education	None			
	Primary/ secondary			
	Tertiary			
Occupation	Unemployed			
	Unskilled			
	Skilled			
Previous pregnancies	Yes			
	No			
Identified cause of infertility	Self			
	Male partner			
	Neither/both/ unknown			
Length of infertility	≤ median			
	> median			
Average monthly family income*	≤ median			
	> median			

**Table 2 T2:** participants diagnosed of depression and anxiety by HADS

Variables	Classes	Anxiety				Depression			
		Control group		Intervention group		Control group		Intervention group	

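### The added survival analysis of HADS remission suits its question poorly: caseness can reverse, is seen only at weeks 3 and 6, and only baseline cases are at risk

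*Protocol article*

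**What the plan says.** All references are to the protocol article, Phase II.

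- **The analysis in question** (Data management and analysis): "Survival analysis will also be carried out at each time to assess number of cases of depression or anxiety that transited to non-cases". The sentence then points to Figure 1. It states no time origin and no rule for a woman who becomes a case again.
- **Visits** (Interventions): "Participants are followed up at three and six weeks; HADS will be administered at both times". With the baseline assessment, that makes three measurements per woman.
- **Eligibility**: "women aged 18 years and above, who have been trying to conceive for at least one year, and who do not have any children". No HADS score is required, so each arm mixes baseline cases and non-cases.
- **Primary outcomes** (Interventions): "primary outcomes are depressive and anxiety symptoms".
- **Score comparison** (Data management and analysis): "Mann-Whitney-U test to compare independent samples of the intervention and control groups at 0, 3 and 6 weeks", which uses both full arms.
- **Table 3**: titled "comparison of the HADS scores between intervention and control groups at 0, 3 and 6 weeks", but its rows are cases and non-cases by arm, with a chi-square test at each visit. It has one set of rows and does not separate anxiety from depression.
- **Figure 1**: not shown in the text at hand; captioned as a "diagram showing flow of participants into cases or non-cases".

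**The concern.** A survival analysis needs an event that happens once and a time at which it happens. This design supplies neither in useful form.

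1. **Time.** A change of state is seen only at a scheduled visit, so an event time can only be 3 or 6 weeks. The times are heavily tied, and each really means some point since the previous visit.
2. **Reversibility.** HADS measures current symptom severity, and a score can cross a cut-off in both directions. A first-remission analysis stops following a woman once she is a non-case and records her as a success whatever her week-6 score shows.
3. **Risk set.** Only a case can become a non-case. Women who are non-cases at baseline do not enter, so worsening among them is invisible in this analysis.

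At stake is the meaning of the remission result. A short-lived response to a single video session, or plain fluctuation around the cut-off, could be reported as recovery, from a part of the randomised sample for which the trial was not sized.

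**Working it through.** **Step 1. The protocol's own figure.** It gives no number for the survival analysis. Its sample size is a two-means calculation: 2 × (1.96 + 0.84)² / 0.53² = 55.8, so 56 per group against the stated 57. The stated 68 follows as 57 × 1.2 = 68.4. Both refer to whole arms.

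**Step 2. Who can contribute.** The article states no case prevalence, so I take 20% to 50% as an assumption. Of 57 evaluable women per arm, 57 × 0.20 = 11.4 to 57 × 0.50 = 28.5 are baseline cases. For an illustrative remission of 30% against 50% (also assumed), the two-proportion power is

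Φ{ [0.20√n − 1.96√(2 × 0.4 × 0.6)] / √(0.3 × 0.7 + 0.5 × 0.5) }.

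This gives 16% at n = 11.4 and 33% at n = 28.5.

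**Step 3. How often first remission is not lasting.** Assumptions: no treatment effect; scores at 0, 3 and 6 weeks trivariate normal with a common correlation r; a cut-off giving the stated prevalence at every visit; 2,000,000 draws. All results are among baseline cases.

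| r | Prevalence | Non-case at week 3 | Of these, case again at week 6 | Ever remitted | Non-case at week 6 | Gap (points) |
|---|---|---|---|---|---|---|
| 0.6 | 20% | 50% | 35% | 68% | 50% | 18 |
| 0.6 | 30% | 42% | 41% | 60% | 42% | 17 |
| 0.6 | 50% | 30% | 50% | 44% | 30% | 15 |
| 0.8 | 20% | 35% | 40% | 50% | 35% | 14 |
| 0.8 | 30% | 30% | 44% | 43% | 30% | 13 |
| 0.8 | 50% | 21% | 50% | 31% | 21% | 10 |

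The gap is the share remitting at week 3 times the share of those who relapse. At r = 0.6 and 30% prevalence that is 0.425 × 0.407 = 0.173. In that setting about 18% of baseline non-cases are cases at week 6, outside the risk set.

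**Step 4. What happens if the effect fades.** Assume remission per interval of 25% (control) and 45% (intervention), with relapse of week-3 remitters by week 6 of 10% and 50%.

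- First remission by week 6: 0.25 + 0.75 × 0.25 = 44% against 0.45 + 0.55 × 0.45 = 70%.
- Non-case at week 6: 0.25 × 0.9 + 0.75 × 0.25 = 41% against 0.45 × 0.5 + 0.55 × 0.45 = 47%.

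With 23 baseline cases per arm (57 × 0.4 = 22.8), a simulated two-visit log-rank test favours the intervention in 45% of runs. The week-6 comparison among the same women does so in 6%.

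**Step 5. False positives.** With equal remission (30%) and equal relapse (20%) in both arms, the log-rank test rejects in about 5% of runs, both directions together. The problem is the question that is answered, not inflated type I error.

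**The case against.** The strongest reply is about scope, and most of it stands. A reader might infer that the trial does not count relapses and new cases at all. The article does not support that. Table 3 compares cases and non-cases by whole arm at every visit, so a woman who relapses or newly becomes a case is in the week-6 count, though not identified as such. The Mann-Whitney tests also use both full arms. The survival analysis is an addition, so the primary score comparison is untouched.

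Three further points deserve weight.

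- **First-event counting is inferred.** The article names no Kaplan-Meier curve, log-rank test or relapse rule, and its reference to each time could mean counting transitions visit by visit. On that reading a relapsed woman is simply a case at week 6. But such a count is not a survival analysis, so the named method would still be the wrong label.
- **A valid version exists.** A discrete-time or interval-censored model of first remission is legitimate if that is the stated question. If relapse does not differ between arms (20% in each, other inputs as in step 4), the log-rank test is the more sensitive: 45% of runs against 34% for the unadjusted week-6 comparison among baseline cases. The method is therefore ill-suited here, not invalid in principle.
- **Figure 1 is not shown.** Its caption describes flow in both directions, and it may already display some transitions.

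Low power in the subset is not a planning error in itself, since the trial was sized for a comparison of two means.

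Nor is this merely detail left to a fuller plan. The article names the method and the event, and a separate analysis plan could add censoring rules but could not create observations between visits or make remission permanent.

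**Conclusion.** The point holds for the supplementary survival analysis only. On its usual reading, that analysis has two possible event times, credits transient remission as success and leaves baseline non-cases outside the risk set. With 20–50% baseline cases and between-visit correlation 0.6–0.8, about 35–50% of week-3 remitters are cases again at week 6, and the ever-remitted share overstates the week-6 non-case share by about 10–18 percentage points.

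These sizes rest on assumed prevalence, correlation and normality, none of which the article gives, and the fading-effect example is one chosen scenario. The finding does not show an inflated false-positive rate or an invalid primary comparison. It is a change that should be made, not one on which the trial depends.

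**What to change.** - Drop the survival analysis.
- Make the week-6 comparison of case status in Table 3 separate for anxiety and for depression. Use logistic regression in all randomised women, adjusted for baseline subscale score and hospital, and report a risk difference with 95% confidence interval.
- Tabulate by arm the four transitions from baseline (case to non-case, case to case, non-case to case, non-case to non-case) at week 3 and at week 6. Label remission among baseline cases as descriptive.

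**Cost.** Analysis-plan wording and a little more modelling; the data are those already collected. The time-to-remission summary is lost, but with two follow-up visits the transition table carries nearly all the information it would have held.

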## Study protocol

### Introduction

Infertility is defined as “a disease of the reproductive system defined by the failure to achieve a clinical pregnancy after 12 months or more of regular unprotected sexual intercourse” [1]. From Demographic and Health Surveys (DHS) from developing countries, one in four couples is affected by infertility [2]. High premium is placed on childbirth in Nigeria; all couples are traditionally expected to procreate. Nigeria's DHS does not report infertility prevalence, however, rural community surveys reported prevalence of 8.7% [3] and 30.3% [4]. Infertility constitutes 24-59% of gynecological consultations in Nigeria [5-8].

Infertile women have feelings of loss, grief, anger, sadness, shame, self-blame and lack of femininity [9,10], which predict actual psychopathology [11]. Though a couple's problem, the woman bears the larger burden of the associated stigma, due to socio-cultural beliefs that reproduction is the woman´s primary responsibility, and a failure is her failing [12,13]. Studies show that infertile women are more likely to be economically disadvantaged [14], suffer psychological distress [15], be socially stigmatized [12,14,16] and suffer intimate partner violence [17], than fertile women. The resulting marital disharmony may lead to divorce, for which the woman is blamed [18]. Infertile men may also have more anxiety and depression symptoms than fertile men [19], but these appear to be less than those suffered by their partners [20].

Nigerian studies have suggested counselling and psychological interventions to ameliorate the documented psychosocial aspects of infertility [15,20,21]. However, no interventional studies were found on the subject. Evidence from outside of sub-Saharan Africa suggests that psychosocial interventions for infertile couples are effective [22-24]. An innovative approach to intervention delivery is the use of eHealth programming, “the use of emerging interactive technologies [e.g. internet, CD-ROMs etc.] to enable health improvement and health care services” [25]. These have the advantage of not requiring facilitators and being reproducible and consistent across time and location.

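### Adverse events are ruled out in advance although the HADS primary outcomes can worsen, and individual worsening is not counted as an outcome or a harm

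*Protocol article*

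**What the plan says.** The last sentences of Data management and analysis (Phase II) deal with safety. They state "A data monitoring committee is not necessary as there are no interventions bordering on patient safety", then "There are no issues that might necessitate termination of trial", and finally "Malfeasance or adverse events are not applicable in a trial that constitutes audiovisual expert education as the intervention".

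The same paragraph gives the analyses:

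- **Scores:** "Interim analysis will be carried out using Mann-Whitney-U test to compare independent samples of the intervention and control groups at 0, 3 and 6 weeks".
- **Transitions:** "Survival analysis will also be carried out at each time to assess number of cases of depression or anxiety that transited to non-cases".

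Reporting of trial results refers to the proportions of cases and non-cases and adds: "The changes in these over 6 weeks will be documented in Table 3 and Figure 1". Table 3 as printed has rows for cases, non-cases and total, by arm and visit, with a chi-square test. Figure 1 is not shown.

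Under Interventions, the primary outcomes are depressive and anxiety symptoms, HADS is given at baseline, 3 weeks and 6 weeks, and feedback is taken straight after the viewing. The Eligibility criteria set no HADS threshold, so women who are non-cases at baseline can enrol.

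**The concern.** The adverse-event sentence is a positive rule and not a gap that another document might fill. It fits poorly with the rest of the protocol. The Introduction describes a vulnerable population, "Infertile women have feelings of loss, grief, anger, sadness, shame, self-blame and lack of femininity", and says that such feelings predict psychopathology. The intervention is a drama on these themes that is meant to change emotional state, and the trial measures that state twice after baseline. The sample-size formula uses 1.96, the two-sided 5% value, so the design itself allows for a difference in either direction.

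The Abstract envisages routine clinic use and community awareness, and the Introduction presents the tool as needing no face-to-face counselling. A reader of the results will want to know whether some women felt worse after viewing. The trial collects the data to answer that, but the plan declares the question irrelevant and names a within-person analysis for improvement only.

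**Working it through.** No figure in the plan decides this point. The question is what each planned analysis can show, so the analyses are set side by side first. Assumed counts then show the size of the gap.

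**1. What each analysis can see**

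| Analysis | Baseline non-cases included? | Net worsening of an arm visible? | Individual worsening counted? |
|---|---|---|---|
| Mann-Whitney U at 0, 3 and 6 weeks | Yes | Yes | No: compares arms visit by visit, without linking a woman's own scores |
| Table 3, chi-square | Yes | Yes, as more cases | No: net counts only |
| Survival analysis, case to non-case | No | No | No |
| Figure 1 | Not shown | Not shown | Not shown |

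A baseline case whose score rises further stays in the cases row of Table 3, so that table cannot show her deterioration. Table 3 as printed also has one block of cases and non-cases, not split into anxiety and depression.

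**2. How net counts hide worsening**

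Inputs: 68 women per arm (Sample size estimation); 30 baseline cases in the arm (assumed), hence 68 − 30 = 38 baseline non-cases; complete follow-up (assumed).

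Cases at 6 weeks = baseline cases − improved + worsened.

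| Improved | Worsened | Cases at 6 weeks | Improved among cases | Worsened among non-cases |
|---|---|---|---|---|
| 10 | 0 | 30 − 10 + 0 = 20 | 10/30 = 33% | 0/38 = 0% |
| 15 | 5 | 30 − 15 + 5 = 20 | 15/30 = 50% | 5/38 = 13% |
| 20 | 10 | 30 − 20 + 10 = 20 | 20/30 = 67% | 10/38 = 26% |

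Suppose the control arm follows the first row and the intervention arm the third. Table 3 then shows 20 cases and 48 non-cases at 6 weeks in both arms. The transition analysis shows 20 improvements against 10 in favour of the video. The 10 new cases in the intervention arm appear nowhere as a count. The Mann-Whitney result would depend on the scores, but opposite movements can cancel there too.

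**3. Whether individual worsening is likely to occur at all**

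The documents give no rate, so a range is assumed. Expected number = 68 × p; chance of at least one = 1 − (1 − p)^68.

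| p (assumed) | Expected per arm | Chance of at least one |
|---|---|---|
| 2% | 1.4 | 75% |
| 5% | 3.4 | 97% |
| 10% | 6.8 | 99.9% |

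Some worsening is likely in either arm, whatever its cause. Only a comparison by arm can say whether the video adds to it.

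**4. Whether Phase I settles the matter**

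The pre-test includes 6 to 10 women with infertility. Even if none of them worsened, the one-sided 95% upper limit, 1 − 0.05^(1/n), is 39% for n = 6 and 26% for n = 10. The pre-test cannot stand in for a harm outcome in the trial.

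**The case against.** The strongest reply is that the plan does look in both directions. A reader might infer from the adverse-event sentence and the survival analysis that only improvement is analysed and that worsening would go unreported. The documents do not support that. The Mann-Whitney comparison at each visit and Table 3 are both two-directional. HADS is given to all participants, and a baseline non-case who becomes a case moves into the cases row at follow-up. A net worsening in the intervention arm would be seen.

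A reader might also infer that all baseline non-cases escape examination; if 50% to 80% of 2 × 68 = 136 women were non-cases, that would be 68 to 109 women. This does not hold either. Those women are outside the survival analysis alone, the percentages are assumed, and Table 2 defines cases separately for anxiety and depression, so no single fraction applies. Figure 1 cannot be used to argue that flow is tracked in one direction: it is not shown, and its caption mentions both states.

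Three further points are fair. The population's distress at entry does not show that the video harms anyone. Participant reaction is not ignored, since feedback follows the viewing and the pre-test invites criticism, although neither is described as recording harm. A points threshold for individual worsening is detail that an analysis plan commonly carries, so its absence here is no fault.

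What the reply does not reach is the sentence itself. It closes the question of harm in advance, and no text shown counts women who moved from non-case to case.

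**Conclusion.** The point holds in a limited form. The protocol declares adverse events inapplicable in a trial whose primary outcomes can themselves deteriorate, and the one within-person transition analysis it names runs towards improvement only. Net worsening of an arm would be visible. Individual worsening offset by improvement in the same arm would be neither counted nor treated as harm, so the trial as written could not support a claim that the video is harmless.

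The size cannot be fixed from the documents. Under the assumed counts above, between 0 and 10 new cases in an arm of 68 are compatible with the same Table 3 entry. The conclusion itself rests only on the wording of the analysis paragraph and the layout of Table 3. It does not affect the efficacy comparison or the sample size, it does not say that the video is harmful, and it does not argue that a data monitoring committee is needed. It is worth correcting because the data will already be in hand.

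**What to change.** Withdraw the statement that adverse events do not apply, and state that worsening on HADS will be reported as a harm outcome.

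Add one table, by arm, at 3 and 6 weeks, separately for anxiety and depression, giving:

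- baseline non-cases who became cases, with the number of baseline non-cases as denominator;
- baseline cases who became non-cases, alongside;
- individual score increases from baseline, as a distribution or above a number of points that the investigators set before seeing the data.

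Note any distress that participants report at the post-viewing feedback and at the 3- and 6-week contacts. Because only the intervention arm has a viewing session, compare arms on the contacts that both share.

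The cost is a rewritten sentence, one table from HADS data already collected, and a short prompt at existing contacts. The sample size is unchanged. How worsening is handled clinically is for the investigators to specify.
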